**Fig. 2 Fig2:**
[figure not shown]
Screenshot of Rango Cards’ interface

The playability of *Rango Cards* is supported by the mechanics of energy. The player has a fixed amount of energy at the beginning of each match and must use it to play the cards. It is worth mentioning that there is no connection between the words “energy” and “calories.” In the first phase, a dynamic tutorial explains the function of energy in the matches. This system is fed back by the player’s choices; thus, the use of healthy food/meal cards is a positive reinforcement and provides rewards (energy) to influence automatic behavior [62]. The cards for foods/meals, dietary practices, and characters are named and subdivided as follows:***Real food***: green cards representing *in natura* (fruits, water, etc.) and minimally processed foods (natural fruit juice, boiled eggs, etc.). They increase the upper energy limit available to the player at the beginning of each turn, i.e., they are crucial to the game.***Prepared meal***: Green cards representing meals cooked on the spot. They are introduced in the third phase, in a restaurant where family recipes passed on from generation to generation are prepared. These cards provide health points, greater attack power, or rewards in the form of new cards, thereby showing the benefits of making healthy choices, especially when eating out.***Industrialized food***: yellow cards representing processed foods (cheese, canned sardine, etc.), which underwent several processes in the food industry and are considered modified versions of the original food [19]. These cards affect sodium, sugar, and/or fat content meters; conversely, they usually have positive effects on the game characters, reinforcing the *Dietary Guidelines* [19] with respect to the need to restrict or consume small portions of these foods.***Mega-industrialized food***: red cards representing foods and meals formulated with an excessive amount of ingredients, which characterizes ultra-processed products. They usually provide the player with some skill to directly harm the opponent or the rival characters, reinforcing the idea that these foods and meals cause health damages. They also affect sodium, sugar, and/or fat content meters.***Characters***: named “Buds” (game buddies), they help the player during the matches by attacking and harming the opponent and the rival Buds or defending the player.***Habit***: cards related to the act of eating and its dimensions, including the importance of choosing appropriate places to buy *in natura* foods; the importance of breakfast; the recommendation of home cooking and eating meals at regular times and clean spaces; the time and attention given to the act of eating; the importance of eating in the company of other people; and the need to critically analyze food advertising and read product labels. These elements reflect the concept of commensality described in the *Dietary Guidelines for the Brazilian Population* [19]. During a match, habits provide the player with benefits such as additional health points, energy or time to play; addition and/or replacement of cards; reversal of negative effects of other cards; and restoration of Buds’ attack power. Figure 3 shows the cards used in *Rango Cards*.

**Fig. 3 Fig3:**
[figure not shown]
Example of cards used in the game

The goal of the game is to make the opponent lose health points, which depends on at least two factors. The first is luck, considering that cards are dealt randomly and there is no predetermination of winning or losing. An exception is the third to last phase, when a new concept is explained and a new card is introduced to the game. The possibility of making choices that lead to different endings and having performance indicators provides autonomy and increases skills and intrinsic motivation [62]. The second factor is the adopted strategy. The player should use the cards logically and spend the energy provided by the cards that allow a longer match time, thus saving as many health points as possible.

*Rango Cards* is divided into seven phases, addressing the following themes: food classification; healthy practices; importance of home cooking; food marketing focused on misleading advertisement; and food label reading. Theme selection and phase order were designed to provide a learning experience. The players are repeatedly exposed to some concepts, as Zajonc recommends [63], encouraging positive food-related attitudes.

The hypothesis is that the game may increase knowledge regarding an adequate and healthy diet as well as self-efficacy in the adoption of healthy practices, which are considered primary outcomes. Secondary outcomes are positive changes in dietary consumption, perceptions, and practices.

#### Preliminary evaluations

To evaluate the game before it was available from application stores, a convenience focus group with seven 1st-year high school students from a Brazilian private school was selected. In this group, impressions about the game and its potential as an educational tool were collected, including the following: *“As you play the game, you learn to develop strategies, eat healthy foods and balanced meals, and sometimes you can use industrialized foods. If you stop to think about it [...], this method is very cool”*; and *“If it was an explanatory thing I wouldn’t play it [...], the cool thing is to understand that if your sugar level is high your health gets worse.”* Qualitative evaluations revealed that the audience was involved, engaged, and interested in the tool, which is essential to the main goal of the game. Adaptations in the mechanics and error adjustments were performed with the purpose of increasing the likelihood of a successful game.

Game management reports from March 2018 informed that *Rango Cards* has been downloaded more than 4050 times after 11 months available from application stores; average rating is 4.9 stars; the most commonly used store is App Store (91%), and the most common device is iPhone (94%). Another positive indicator is that *Rango Cards* was awarded the Best Serious Game in the SBGames 2017, the greatest Latin American academic event in the field of games and digital entertainment.

#### Intervention group

Adolescents in the intervention group will be instructed to play the game, and the first contact will occur at the school. Because of its autonomous nature, the intervention will not be included in the school curriculum. To increase the intervention group’s motivation, an environment of challenge and social interaction will be created among the students of each school, based on a competition of time spent to finish the game. These aspects are considered important by adolescents who play games [33, 62, 64]. The students will be able to play *Rango Cards* at school and also at the time and place which are more convenient for them. The period to play will be 3 weeks, and then a post-intervention questionnaire will be applied. This autonomy, which reflects “the will to perform a task,” aims to improve intrinsic motivation [64].

#### Control group

Adolescents in the control group will not be instructed to play the game nor will receive any healthy diet material, i.e., the researchers will not provide them with any additional material during the study.

#### Measures

Both groups will complete research questionnaires before and after the nutritional intervention. The following variables will be investigated: age, sex, family income, maternal level of education, dietary perceptions and practices, food knowledge, and self-efficacy in the adoption of healthy practices. Family income and maternal level of education will be evaluated using questions from population surveys performed in Brazil periodically [65]. Dietary perceptions will be based on a scoring system in which participants will evaluate how healthy their diet is and how much they know about the topic. Dietary practices will be assessed using the weekly frequency of consuming healthy (beans, vegetables, and fruits) and unhealthy foods (ultra-processed foods, fried snacks, soft drinks, sweets, and fast food), the frequency of having breakfast, lunch, or dinner with parents or legal guardians, and the frequency of eating while watching TV or studying [3]. Food knowledge and self-efficacy in the adoption of healthy practices will be based on the content of the game and on items from previous studies with adolescents and young adults [13, 66, 67]. The participants will be asked to analyze some statements and express their level of agreement using a 5-point Likert-type scale.

The questionnaires will be completed and supervised by at least two researchers. Pre- and post-intervention questionnaires will comprise the same questions, except for the sociodemographic variables, which will be investigated only at the first moment. The instruments will be previously tested in a convenience sample of adolescents who will not be included in the main study. This activity will assess clarity and comprehension of each question, providing an analysis of structural items such as language, progressive logic, question order, and writing strengths and/or weaknesses. The necessary adjustments will be performed before the beginning of the main study.

#### Data analysis

After data collection, the questionnaires will be entered into electronic spreadsheets. To ensure data reliability, data will be double entered. Sociodemographic variables will be analyzed descriptively and expressed as mean, standard deviation, and frequencies. The Pearson’s chi-squared test will be used for sex and age, while the Mann-Whitney U test will be used for family income and maternal level of education. To assess the impact of the intervention, unpaired analyses will be performed using the Student’s t-test for continuous numerical variables (dietary perceptions) and Likert-type scales (food knowledge and self-efficacy). The Mann-Whitney U test will be used for dietary practices and food consumption. The significance level will be set at 5%, and the statistical analyses will be performed using the Statistical Package for the Social Sciences (SPSS), version 21.0.

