#### Sample size and recruitment

The sample size was calculated considering the prediction of a 1.5 point increase in the food knowledge score after the intervention, with a standard deviation of 2.9 [58], a significance level of 5%, and power of 80%. Under these conditions, the minimum sample should be of 60 individuals per group, with control of the participants’ gender. Adding an estimated 40% loss between the pre- and post-intervention moments, the minimum total sample is defined as 168 individuals (84 per group). Each class in private schools has approximately 35 students [57]. Considering an estimate enrollment of 21 participants per class (40% of refusal), we expect to enroll 8 schools in the study, which will be randomly selected to form the study groups: 4 in the intervention group and 4 in the control group.

To recruit the selected school units, we will use email, telephone, and in-person visits to contact each school and explain our research. After the schools agree to participate and sign a consent form, we will select 1st-year high school classes and schedule visits to explain the study to students. Those who verbally agree to participate will be asked to request the written consent of their parents or legal guardians. Finally, the students’ assent will be obtained. Figure 1 shows the flowchart of recruitment and intervention of the study.

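### The t-test for both primary outcomes has no place for baseline score or sex and does not say whether post or change scores are compared; a baseline-adjusted model would be more precise.

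*Protocol article*

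**What the plan says.** Under Data analysis, the protocol article fixes the test of effect: "To assess the impact of the intervention, unpaired analyses will be performed using the" Student's t-test, applied to dietary perceptions and to the Likert-type scales for food knowledge and self-efficacy. The Game components section names knowledge and self-efficacy as the primary outcomes. Sex appears under Data analysis only in a chi-squared test among the sociodemographic variables.

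Three other statements bear on this test:

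- Measures: "Both groups will complete research questionnaires before and after the nutritional intervention". The two questionnaires carry the same questions apart from the sociodemographic items, so each student who completes both has a baseline value of each primary outcome. Sex is recorded at the first visit.
- Sample size and recruitment: the calculation rests on "the prediction of a 1.5 point increase in the food knowledge score after the intervention", "with a standard deviation of 2.9", and is said to be done "with control of the participants’ gender".
- The same section forms the groups from 8 schools, 4 per arm, with about 21 students each.

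**The concern.** The design collects a baseline score and sex and claims control of gender, but the two-sample test that is named takes neither as a covariate. A chi-squared comparison of sex between the arms describes balance; it does not adjust the effect for sex.

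The text also leaves open which variable is tested. An unpaired t-test could compare post scores or changes from baseline, and these are different estimators with different standard errors. With only 8 schools allocated, chance differences in baseline knowledge between the arms can be sizeable. How far they reach the effect estimate depends on which of the two is meant. Both primary outcomes are affected.

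This is not a detail that the article leaves to a fuller document. It states the test, and the test as stated has no covariate.

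**Working it through.** **Inputs from the protocol article (Sample size and recruitment).** Difference 1.5; SD 2.9; "a significance level of 5%, and power of 80"%; 60 per group, raised to 84 per group for 40% loss; 4 schools per arm; 21 students per school. The article does not say whether 2.9 is the SD of the post score or of the change.

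**Assumed, because not given.** Pre-post correlation r (0.5 to 0.7 shown); intraclass correlation, ICC (0.02 to 0.10); equal SDs before and after; the same r within and between schools; two-sided testing.

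**Step 1. The plan's own figure.** n per group = 2 × (1.960 + 0.842)² × 2.9² / 1.5² = 58.7, so 59 by the normal approximation. The exact t calculation gives 60 with power 0.802. The stated figure ("the minimum sample should be of 60 individuals per group") is therefore reproduced as an unadjusted two-sample comparison. Neither baseline nor sex enters it.

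**Step 2. Chance baseline difference between arms.** SD = 2.9 × √(2 × (1 + 20 × ICC) / 84), taking 2.9 as the SD of a single score. In an unadjusted post-score comparison about r times this difference passes into the estimate.

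| ICC | SD of baseline difference | Part carried over at r = 0.5 |
|---|---|---|
| 0.02 | 0.53 | 0.26 |
| 0.05 | 0.63 | 0.32 |
| 0.10 | 0.78 | 0.39 |

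Against the 1.5-point target, the carried-over SD is 0.26/1.5 = 17% to 0.39/1.5 = 26%.

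**Step 3. Residual variance with baseline adjustment (ANCOVA).**

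- Against a post-score test, the variance is multiplied by 1 − r²: 0.75 at r = 0.5, 0.64 at r = 0.6, 0.51 at r = 0.7.
- Against a change-score test, it is multiplied by (1 + r)/2: 0.75 at r = 0.5, 0.80 at r = 0.6, 0.85 at r = 0.7.

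The two readings agree at r = 0.5 and move in opposite directions above it.

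**Step 4. Individual-level power, ignoring schools.** Completers per group: 84 × 0.6 = 50.4. Exact t:

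| Analysis | 2.9 is post-score SD | 2.9 is change-score SD |
|---|---|---|
| Unadjusted test | 73% | 73% |
| ANCOVA, r = 0.5 | 84% | 84% |
| ANCOVA, r = 0.6 | 90% | 82% |
| ANCOVA, r = 0.7 | 95% | 80% |

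**Step 5. The same comparison allowing for schools.** Completers per school: 50.4/4 = 12.6. At ICC 0.05 the design effect is 1 + 11.6 × 0.05 = 1.58. With a school-level test on 8 − 2 = 6 degrees of freedom and 2.9 as the post-score SD, power is about 41% unadjusted, 52% at r = 0.5 and 58% at r = 0.6. Adjustment still helps, but the absolute level is far below the Step 4 figures.

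**The case against.** The strongest reply is that the article may intend an unpaired t-test on change scores. The sample size section speaks of an increase after the intervention, the same items are asked twice, and a between-arm test of change fits the word unpaired. A reader might infer from the Data analysis section that the baseline score is ignored altogether. The documents do not support that as fact; they support only that the analysed score is not named. Nor do they support reading the plan as an unpaired comparison of pre with post within an arm. This objection limits the point but does not remove it: on the change-score reading ANCOVA variance is still (1 + r)/2 of the change-score variance, and sex still has no place in the test.

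A second reply is that an unadjusted comparison between randomised groups is unbiased on average, so the baseline difference is ordinary sampling error. That stands. It would also be wrong to treat the whole baseline difference (SD 0.53 to 0.78) as error in the effect, since only about a fraction r carries over.

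A third reply concerns the power figures. A reader might infer that the design would reach 84% to 90% once adjusted. It would not: those figures ignore clustering, and the 90% further assumes r = 0.6 and that 2.9 is the SD of the post score. The 73% starting point also reflects how 60 was raised to 84 (60 × 1.4), which is a separate matter; at 60 per group the unadjusted test has 80%.

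Finally, control of gender might mean balance by design. The article describes no such device, and the test does not supply the control either way.

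**Conclusion.** The point holds in this form: for both primary outcomes the article fixes an unpaired t-test without covariates, does not say which score is compared, and does not carry out in the analysis the gender control that it states for the sample size.

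The cost is lost precision and exposure to chance imbalance, not systematic bias. At r = 0.5 the residual variance is 25% lower with baseline adjustment on either reading; at higher r the gain grows against a post-score test and shrinks against a change-score test. If post scores are compared, the chance imbalance passed into the estimate has an SD of about 0.26 to 0.39 points at r = 0.5 and ICC 0.02 to 0.10.

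The size rests on r and ICC, which the article does not give, and on what the 2.9 measures. The direction does not depend on the ICC or on that SD: for r between 0 and 1, both variance factors in Step 3 are below 1. The change should be made. It does not by itself make the design adequately powered, because school clustering remains to be dealt with.

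**What to change.** In Data analysis, replace the t-test for food knowledge and self-efficacy with a regression of each post score on arm, the student's own baseline score and sex. The model should account for school and use a small-sample correction suited to 8 schools. Report the adjusted difference with its 95% confidence interval. If a change-score or post-score t-test is kept as a supporting analysis, name the score.

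In Sample size and recruitment, state whether 2.9 is the SD of the post score or of the change, and what control of gender means. If credit is taken for baseline adjustment, state the assumed r and give power with clustering included.

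The cost is wording only: baseline scores and sex are already collected.

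### Schools are the only unit whose allocation is described, but outcomes are tested student by student, so type I error exceeds 5% for any positive within-school correlation

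*Protocol article*

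**What the plan says.** **Allocation.** The section Sample size and recruitment of the protocol article expects to enrol 8 schools, "randomly selected to form the study groups: 4 in the intervention group and 4 in the control group". Classes and then students are recruited inside the schools that agree. No section describes random allocation of students.

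**Primary outcomes.** The end of the section on game components names knowledge of an adequate and healthy diet together with "self-efficacy in the adoption of healthy practices, which are considered primary outcomes". Both are measured on individual students, before and after the intervention.

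**Analysis.** To judge the effect of the game, the section Data analysis sets an unpaired comparison by "t-test for continuous numerical variables (dietary perceptions) and Likert-type scales (food knowledge and self-efficacy"), the test being Student's. For the remaining outcomes it adds this rule: "The Mann-Whitney U test will be used for dietary practices and food consumption". The significance level is 5%. The section mentions no school or class effect, no ICC and no school-level summary.

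**Delivery.** In the intervention schools, "an environment of challenge and social interaction will be created among the students of each school", through a competition on the time taken to finish the game.

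**The concern.** A student-level t-test or Mann-Whitney test treats every student as a separate piece of evidence about the game. Here all students in a school receive the same allocation, so differences between schools that have nothing to do with the game enter the group comparison in full. With four schools per group there is little chance that they average out. The planned tests estimate the standard error only from the spread among students and so understate it. Confidence intervals become too narrow and p-values too small, including for both primary outcomes. A significant result could then reflect which schools fell into which group.

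The document itself gives reasons to expect some correlation within schools. Its Background says that eating behaviour depends on the dietary environment and on social and cultural conditions, and its Discussion says that social or environmental factors may affect acceptance of the game.

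**Working it through.** **Inputs from the document (Sample size and recruitment).** Difference 1.5 points, SD 2.9, significance level 5%, power 80%, 60 evaluable per group, 84 enrolled per group, 21 enrolled per class, 8 schools (4 per group), 40% loss.

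**Students per school, m.** Enrolled: 84/4 = 21. At the evaluable target: 60/4 = 15. After 40% loss from 21: 21 × 0.6 = 12.6, taken as 13.

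**Assumption.** The document gives no ICC. The values 0.01, 0.02, 0.05 and 0.10 are assumed.

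**Step 1: reproduce the stated sample size.** For independent individuals, n per group = 2 × (1.960 + 0.842)² × 2.9² / 1.5² = 58.7, so 59. The t-based solution is 59.65, so 60. The stated 60 is therefore a two-sided calculation for independent students (one-sided gives 47). It contains no allowance for clustering.

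**Step 2: type I error of the student-level test.** Design effect DE = 1 + (m − 1) × ICC. Actual error at nominal 5% = 2 × [1 − Φ(1.96/√DE)].

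Example with m = 15 and ICC 0.05: DE = 1 + 14 × 0.05 = 1.70, 1.96/√1.70 = 1.503, error = 13.3%.

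| ICC (assumed) | m = 13: DE, error | m = 15: DE, error | m = 21: DE, error |
|---|---|---|---|
| 0.01 | 1.12, 6.4% | 1.14, 6.6% | 1.20, 7.4% |
| 0.02 | 1.24, 7.8% | 1.28, 8.3% | 1.40, 9.8% |
| 0.05 | 1.60, 12.1% | 1.70, 13.3% | 2.00, 16.6% |
| 0.10 | 2.20, 18.6% | 2.40, 20.6% | 3.00, 25.8% |

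**Step 3: check by simulation.** Four schools per arm, normal data, no intervention effect. The student-level t-test (20,000 runs) rejected in 6.7%, 8.6%, 13.3% and 21.0% of runs for m = 15 at the four ICCs, close to the formula. The Mann-Whitney test (3,000 runs) gave 6.4%, 8.1%, 12.4% and 18.7%. A t-test on the 8 school means (6 df) stayed between 4.9% and 5.3% over the same four cases.

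**Step 4: power of the valid test.** Variance of a school mean = 2.9² × [ICC + (1 − ICC)/15]. Noncentrality = 1.5/√(2 × variance/4), with 6 df and critical t 2.447.

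| ICC | Variance of school mean | Noncentrality | Power |
|---|---|---|---|
| 0 | 0.561 | 2.83 | 66% |
| 0.01 | 0.639 | 2.65 | 60% |
| 0.05 | 0.953 | 2.17 | 45% |
| 0.10 | 1.346 | 1.83 | 34% |

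Even at ICC 0 the power is below 80%, because only 8 units remain and the test has 6 df.

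**The case against.** **The size is not known.** A reader might infer that the false-positive rate is well above 5% whatever the data look like. The document does not support that, because it gives no ICC. At 0.01 the error is only 6.4% to 7.4%. The description fits from about 0.05 upward. What stands without condition on size is the direction: above 5% for any positive ICC.

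**Change scores may reduce the correlation.** Questionnaires are given before and after, and the sample size rests on an increase in score. If the unpaired tests are applied to changes, stable differences between schools largely cancel and the relevant ICC may lie at the low end. This is fair. It lessens the problem but does not remove it, because schools can also differ in how much their students change.

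**The competition is weak evidence for type I error.** It takes place only in the intervention schools. If the game changed no student's score, it would create no correlation under the null hypothesis. It bears more on precision when there is an effect.

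**The text could be condensed.** An article may leave detail to a fuller plan. Here, however, the tests, the level and the software are named, and the named tests do not fit the allocation described. The phrase "8 schools in the study, which will be randomly selected to form the study groups" is loose, but it cannot be read as allocation of students.

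**Conclusion.** The concern holds in conditional form. The analysis as written does not match the only allocation described, and its type I error exceeds 5% for any positive within-school correlation. With 13 to 21 students per school the error is about 6% to 7% at ICC 0.01, rising to 19% to 26% at ICC 0.10. These sizes rest on the assumed ICCs, on equal school sizes and, for the simulations, on normal data. Both primary outcomes are affected, so the analysis section should be corrected before the data are analysed. The stated 80% power has the same origin, since it assumes independent students, and it cannot be carried over to a valid analysis of 8 schools.

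**What to change.** - Describe the trial as cluster-randomised, with school as the unit of allocation.
- For food knowledge, self-efficacy and dietary perceptions, use a linear mixed model with a random school intercept and Satterthwaite or Kenward-Roger degrees of freedom, or a t-test on the 8 school means (6 df). Report the ICC for each outcome.
- For dietary practices and food consumption, replace the student-level Mann-Whitney test with school-level summaries compared in the same way.
- A permutation test over the C(8,4) = 70 allocations is an alternative only if randomisation was unrestricted, which the document does not state. Its two-sided p-values go from 2/70 = 0.029 to 4/70 = 0.057, so only the most extreme split can reject at 5%. If schools were matched in pairs there would be 2⁴ = 16 allocations and a smallest p of 2/16 = 0.125.
- Restate the power with an ICC and its source.

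**Cost.** Validity needs only a rewritten analysis section and modest extra work, with no new data. The real cost is power: with 8 schools and 15 evaluable students in each, 60%, 45% and 34% at ICC 0.01, 0.05 and 0.10. To reach 80% at that school size, about 6, 8 and 11 schools per arm would be needed. If more schools cannot be added, the lower power should be stated openly.
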